## Abstract

**Background:**

Institutionalized older persons have a poor functional capacity. Including physical exercise in their routine activities decreases their frailty and improves their quality of life. Whole-body vibration (WBV) training is a type of exercise that seems beneficial in frail older persons to improve their functional mobility, but the evidence is inconclusive. This trial will compare the results of exercise with WBV and exercise without WBV in improving body balance, muscle performance and fall prevention in institutionalized older persons.

**Methods/Design:**

An open, multicentre and parallel randomized clinical trial with blinded assessment. 160 nursing home residents aged over 65 years and of both sexes will be identified to participate in the study. Participants will be centrally randomised and allocated to interventions (vibration or exercise group) by telephone. The vibration group will perform static/dynamic exercises (balance and resistance training) on a vibratory platform (Frequency: 30-35 Hz; Amplitude: 2-4 mm) over a six-week training period (3 sessions/week). The exercise group will perform the same exercise protocol but without a vibration stimuli platform. The primary outcome measure is the static/dynamic body balance. Secondary outcomes are muscle strength and, number of new falls. Follow-up measurements will be collected at 6 weeks and at 6 months after randomization. Efficacy will be analysed on an intention-to-treat (ITT) basis and 'per protocol'. The effects of the intervention will be evaluated using the "t" test, Mann-Witney test, or Chi-square test, depending on the type of outcome. The final analysis will be performed 6 weeks and 6 months after randomization.

**Discussion:**

This study will help to clarify whether WBV training improves body balance, gait mobility and muscle strength in frail older persons living in nursing homes. As far as we know, this will be the first study to evaluate the efficacy of WBV for the prevention of falls.

**Trial Registration:**

ClinicalTrials.gov: NCT01375790

## Background

Progressive ageing of the population has generated an increase in chronic diseases [1]. The concomitant increases in morbidity create vulnerability and frailty in older persons.

Frailty is a common syndrome in older persons [2]. Signs and symptoms of this problem are believed to factors such as fatigue, weight loss, exhaustion, weakness, slow walking speed, decreased balance, low levels of physical activity, slowed motor processing and performance, social withdrawal, cognitive changes, and increased vulnerability to stressors [3-6].

Most falls in older persons are caused by frailty [7,8] and multiple medications [9-11]. Research from the United Kingdom [12], the United States [13] and Australia [14] has shown that falls are a tremendous burden to social and health services. Besides affecting psychological and physical health, fractures from falls often imply hospitalization, thereby increasing morbidity. It has been estimated that total health costs attributable to fall-related injuries will practically triple in the next 50 years. Strategies to prevent the negative consequences of falls are needed. One such strategy is exercise [15,16].

Institutionalized older people have less capacity to exercise, and greater osteoarticular deterioration and fatigue than non-institutionalized older people [3]. Improving their physical activity could increase their autonomy and help prevent falls [17-23]. Fighting sedentary attitudes and promoting physical exercise are growing challenges for physiotherapists and other health professionals working in nursing homes.

Whole body vibration is a type of physical exercise that consists of performing static and dynamic exercises on a platform. These effects of this type of exercise have been studied previously in two studies in nursing home residents [24,25]. The results of these interventions were not conclusive because there are differences in the study protocols and limitations in the study designs. Both studies analysed functional capacity and muscle performance but neither recorded the number of falls.

The aim of the present study is to assess the effect of whole-body vibration training on body balance comparing to exercise without vibration in institutionalized older persons. Secondarily, we will evaluate the effects of training on muscular strength and prevention of falls in this population.

## Methods/design

### Study design

This study will be an open randomized, multicentre, and parallel clinical trial with evaluator-blinded. The details of this protocol are reported with CONSORT Statement [26]. Figure 1 presents the flow diagram of the study design. The study protocol was approved by the Ethic Committees of the *Corporació Sanitària Parc Taulí de Sabadell *and, the *Hospital Universitari Mútua de Terrassa*, Spain.

**Figure 1 F1:**
[figure not shown]
**Flow diagram of the study design**.

### Interventions

Participants will be randomized to an experimental group (WBV group) or to a control group (exercise group). Participants in the WBV group will perform static/dynamic exercise (balance and resistance training) on a vibratory platform (Frequency: 30-35 Hz; Amplitude: 2-4 mm; Pro5 Airdaptive Model, Power Plate^®^, The Netherlands). Participants in the exercise group will performed the same static/dynamic exercises (balance and resistance training) as the WBV group but without the vibratory platform. Training will consist of 3 sessions per week over 6 weeks. Training volume will be increased progressively over this period. To prevent learning problems at the beginning of the training period, participants will receive an introductory practice session to become familiar with positioning on the vibration platform before the first session [27].

The physiotherapists from each nursing-home will be previously instructed about the study. Three external physiotherapists will verify therapeutic compliance once a week during the intervention and will provide any support needed.

### Follow-up

All tests will be performed at baseline, at 6 weeks (at the end of the intervention

period), and 6 months after the end of the study (Figure 1).

Data concerning falls will be regularly collected from each nursing-home or from relatives if a participant moves to another address.

### Outcome measures

The outcome assessment will be blinded. The two physiotherapists trained in the evaluation procedure will not know the allocation to intervention.

#### Primary outcome

##### • Body Balance

Body balance outcome will be assessed using the Tinetti test [28] and the Timed Up & Go test (TUG) [29].

The Tinetti test has 16 items: 9 for body balance and 7 for gait. The score for each exercise ranges from 0 to 1 or 0 to 2. A lower score indicates poorer physical ability. The global score is 28: 16 is the maximum score for body balance and 12 is the maximum one for gait.

The Timed Up & Go test also assesses functional mobility. Participants stand up from a chair, walk 3 m as quickly and safely as possible, cross a marked line on the floor, turn around and then walk back and sit down in the chair [29]. The chair will be adjusted to the height of each person and will be fixed to the wall. The time taken to complete the task will be recorded.

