### Sample size

We calculated sample size was calculated assuming a difference of 5 points (SD 10) between the groups in the Tinetti test at the end of intervention. We considered a two-sided alpha level of 0.05, a statistical power of 80%, and 20% of losses [24,32]. The total number of estimated cases was 160 (80 in each group).

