### Statistical methods

Efficacy will be analysed on an intention-to-treat (ITT) basis. Additionally, a 'per protocol' analysis will be performed. Missing values will be assigned the last available valid score. We will evaluate the effects of the intervention on each quantitative, qualitative and ordinal outcome using the "t" test, Mann-Witney test or the Chi-square test, depending on the type of outcome. The final analysis will be performed 6 weeks and 6 months after randomization. The number of falls over the 6-month period will be recorded.

Changes in body balance and muscle performance will be analysed 6 weeks and 6 months after starting the study using a two-way analysis of variance (ANOVA). Factors included will be the group (vibration or exercise group) and the time (at baseline and after six weeks of intervention), and the interaction between them. The software used will be SPSS17.

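### The trial is sized on Tinetti at the end of the intervention, but two tests and two final time points share primary status, so the plan does not secure its 5% error rate

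*Protocol article*

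**What the plan says.** All references are to the protocol article.

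- The Abstract names a construct, not a measure at a time point: "The primary outcome measure is the static/dynamic body balance".
- The Body Balance entry under Primary outcome names two instruments on an equal footing: "Body balance outcome will be assessed using the Tinetti test [28] and the Timed Up & Go test (TUG").
- Statistical methods, like the Abstract, gives two final time points: "The final analysis will be performed 6 weeks and 6 months after randomization". Each outcome gets its own test, chosen by outcome type. A two-way ANOVA is added: "Changes in body balance and muscle performance will be analysed 6 weeks and 6 months after starting the study".
- Sample size uses a single comparison, a 5-point difference (SD 10) "between the groups in the Tinetti test at the end of intervention". On error and power it says "We considered a two-sided alpha level of 0.05" and "a statistical power of 80%, and 20% of losses". The result is 160 participants, 80 per group.

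**The concern.** The section that fixes error rate and power treats the trial as having one endpoint. The sections that define the outcome and its analysis leave four comparisons (two instruments at two time points), any of which could be presented as the balance result. No sentence links the two by naming the comparison that decides the trial.

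Two things are at stake. First, the 0.05 in the sample size applies to one comparison and says nothing about the chance of a false balance claim when the choice among four is open. Second, discordant results have no agreed reading in this document. Tinetti could be null with Timed Up & Go positive, or the groups could differ at 6 weeks but not at 6 months. The headline could then be chosen after the data are seen.

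**Working it through.** **1. The plan's own figure.** Inputs from Sample size: difference 5, SD 10, two-sided alpha 0.05, power 80%, losses 20%.

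Normal approximation, per arm: n = 2(z₀.₉₇₅ + z₀.₈₀)² × SD² / difference² = 2 × (1.960 + 0.842)² × 100/25 = 62.8, so 63. The t-test version gives 63.8, so 64. Allowing for losses: 64 / 0.8 = 80 per arm, 160 in total. The stated figure is reproduced exactly, for one comparison at 0.05.

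**2. How many comparisons can claim the primary result.** Two instruments × two final time points = 4. The per-protocol analysis and the ANOVA run alongside the simple tests are not counted.

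**3. False-positive chance if any one of the four suffices.** This decision rule is an assumption. Each comparison is tested at two-sided 0.05 with no true difference anywhere.

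Independent: 1 − 0.95⁴ = 0.185.

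Correlated: probability that at least one of four standard normal statistics exceeds 1.96 in absolute value, from 1,000,000 simulated draws. The documents give no correlations, so a range of common values is shown:

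- r = 0.3: 17.4%
- r = 0.5: 15.6%
- r = 0.7: 13.0%
- r = 0.9: 9.4%

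Letting the correlation between tests differ from that between times, with the cross-correlation as their product, gives similar results: 14.9% for 0.5 and 0.7, and 12.0% for 0.8 and 0.8.

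**4. The two instruments at 6 weeks only.** Independent: 1 − 0.95² = 0.0975. Simulated: 9.0% at r = 0.5, 8.3% at r = 0.7, 7.8% at r = 0.8 and 7.1% at r = 0.9. So it is about 8–10% unless the correlation is very high.

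**5. What the alternatives cost** (5 points, SD 10, 64 evaluable per arm, normal approximation).

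- One named primary, the one already sized: error 5%, N = 160 unchanged.
- Both instruments primary at 6 weeks under Holm: the first step is at 0.025. The standardised difference is 5 / (10 × √(2/64)) = 2.83, so power for Tinetti at that step is Φ(2.83 − 2.24) ≈ 72%. Restoring 80% at that level needs 2 × (2.241 + 0.842)² × 4 = 76.04, so 77 evaluable per arm. Then 77 / 0.8 = 96.25, so 97 per arm and 194 in total.
- All four kept at 0.05/4 = 0.0125 each: power is about 63%. Restoring 80% needs 90 evaluable per arm. Then 90 / 0.8 = 112.5, so 113 per arm and 226 in total.

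**The case against.** The best reply is that the protocol already shows which endpoint is meant. Sample size uses Tinetti at the end of the intervention, and the time factor of the ANOVA lists only baseline and six weeks. Read that way there is one primary test and the error rate is 5%. This is good evidence of intent, and it is why the fix below is the natural one. It does not settle the matter. The endpoint used for sizing is never declared primary, Timed Up & Go has the same status under Primary outcome, and the sentence introducing the ANOVA covers both 6 weeks and 6 months.

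Three stronger readings are tempting, and the document does not support them.

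- A reader might infer that the trial's true error rate is some definite figure, such as 13–17%. That needs both a rule that any one significant comparison suffices and a particular set of correlations, and the protocol gives neither. If both instruments had to be significant at a given time point, the error there would be at most 5%, and the price would be power.
- A reader might count the 16-point balance and 12-point gait parts of the Tinetti test as further primary tests. The protocol mentions them only to explain the scoring and does not declare them as outcomes.
- A reader might treat the lack of a multiplicity procedure as the defect. In a condensed article that can be left to an analysis plan that is not shown. Which measure and time point are primary is a protocol decision, and this document does address it, in a way that does not match its own sizing.

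**Conclusion.** The point holds as a mismatch within the protocol: one comparison is sized at 5%, while two instruments and two final time points are left able to support the primary conclusion. What the text supports is that the plan does not secure 5%, not that the error rate is known to be higher.

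The size is conditional. If any one of four comparisons counts, the error is 18.5% under independence and about 9–17% for assumed common correlations from 0.9 to 0.3. With the two instruments at 6 weeks only, it is about 8–10%. With Tinetti at 6 weeks alone, it is 5%. The sample size arithmetic is correct and is not in question. The choice should be made before any comparative results are seen, because it cannot be made credibly afterwards.

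**What to change.** State in the Primary outcome section, and match it in the Abstract and Statistical methods, that the single primary endpoint is the Tinetti global score (0–28) at the end of the 6-week intervention, tested at two-sided 0.05. Sample size refers only to the Tinetti test, so the sponsor should confirm that the global score is the one meant. Make Timed Up & Go and all 6-month results secondary, reported with estimates and 95% confidence intervals.

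This is a change of wording. No measurement is dropped and N = 160 stands. The small downside is that a positive Timed Up & Go or 6-month result cannot carry the headline alone.

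If the sponsor wants both instruments to stay primary at 6 weeks, apply Holm and restate the power. For Tinetti it is about 72% at the 0.025 first step with 64 evaluable per arm, and about 194 participants would be needed to restore 80% at that step.

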#### Secondary outcomes

##### • Muscle Performance

Muscle performance will be evaluated using five repetitions of the Sit-to-Stand test [30,31]. Subjects will be asked to stand up and sit down five times, as quickly as possible, with their arms folded across the chest. The chair will be adjusted to the height of each person and will be fixed to the wall. The time taken to complete the task will be recorded by chronometer. The maximum speed of each repetition and the average speed will be recorded using the Smart Coach encoder.

##### • Number of falls

Any falls during the study will be recorded in a fall register developed specifically for the study.

### Sample size

We calculated sample size was calculated assuming a difference of 5 points (SD 10) between the groups in the Tinetti test at the end of intervention. We considered a two-sided alpha level of 0.05, a statistical power of 80%, and 20% of losses [24,32]. The total number of estimated cases was 160 (80 in each group).

### Randomization

A computer generated randomization list will be generated for participants at each nursing-home using the statistical software SPSS17. Allocation to treatment will be centralized by telephone. All the researchers will be blinded to the randomization sequence list.

### Statistical methods

Efficacy will be analysed on an intention-to-treat (ITT) basis. Additionally, a 'per protocol' analysis will be performed. Missing values will be assigned the last available valid score. We will evaluate the effects of the intervention on each quantitative, qualitative and ordinal outcome using the "t" test, Mann-Witney test or the Chi-square test, depending on the type of outcome. The final analysis will be performed 6 weeks and 6 months after randomization. The number of falls over the 6-month period will be recorded.

Changes in body balance and muscle performance will be analysed 6 weeks and 6 months after starting the study using a two-way analysis of variance (ANOVA). Factors included will be the group (vibration or exercise group) and the time (at baseline and after six weeks of intervention), and the interaction between them. The software used will be SPSS17.

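### Last observation carried forward is the only stated missing-data rule; it does not match a sample size that treats the 20% lost as removed, and it can cost power at 6 weeks and bias the 6-month comparison

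*Protocol article*

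**What the plan says.** The protocol article, Statistical methods, sets an intention-to-treat analysis with a per-protocol analysis beside it, and states one rule for gaps: "Missing values will be assigned the last available valid score". The rule is not limited to any outcome or visit. The completed data then go into t, Mann-Whitney or chi-square tests and into a two-way ANOVA on changes with a group-by-time interaction.

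The Sample size section plans the trial "assuming a difference of 5 points (SD 10) between the groups in the Tinetti test at the end of intervention" and continues: "We considered a two-sided alpha level of 0.05, a statistical power of 80%, and 20% of losses". The result is 160 residents, 80 per group. The timing, arm and reasons of the losses are not given.

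The Follow-up section places assessments at baseline, at 6 weeks and at a later 6-month visit. For the Timed Up & Go, part of the primary outcome, the Body Balance section says "The time taken to complete the task will be recorded". The five-repetition Sit-to-Stand is also a timed test.

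**The concern.** The sample size and the analysis treat the same residents in two different ways. The inflation for losses assumes that one in five residents contributes nothing and that the rest show the full 5-point difference. The carry-forward rule keeps all 80 per arm and gives the missing ones an old score.

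Three consequences follow from the rule as written:

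- **At 6 weeks** the last valid score can only be baseline. Randomised groups have no expected difference there, so each filled value pulls the contrast towards zero.
- **At 6 months** the last valid score is usually the one taken straight after training. The rule assumes that any gain persists unchanged in exactly the residents no longer measured. If scores drift down after training and one arm loses more residents, that arm looks better without any treatment effect.
- **For the timed tests**, a resident who attends but cannot finish has no time to record. Read literally, the rule supplies an earlier successful time, so a loss of function is scored as stability.

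The filled values also enter every test as if they had been measured. At stake are the power of the primary comparison and the false-positive rate of the 6-month comparison.

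**Working it through.** **1. The plan's own figure.** Inputs from the Sample size section: difference 5, SD 10, two-sided alpha 0.05, power 80%, losses 20%. The standardised difference is 5/10 = 0.5. The two-sample t-test needs 63.8, so 64 per arm, with power 80.1%. Inflating for losses, 64/(1 − 0.20) = 80 per arm, 160 in total. The stated figure reproduces exactly. This inflation is right if the lost residents leave the analysis.

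**2. The same inputs under carry-forward at 6 weeks.** Let *d* be the share lost before week 6, equal in both arms. Those observed differ by 5 and those filled from baseline by 0, so the expected difference is 5 × (1 − *d*). All 80 per arm stay in the test. With SD 10:

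| Lost before week 6 | Expected difference | Power (t-test, 80 per arm) |
|---|---|---|
| 0% | 5.00 | 88.2% |
| 5% | 4.75 | 84.8% |
| 10% | 4.50 | 80.8% |
| 15% | 4.25 | 76.2% |
| 20% | 4.00 | 71.0% |

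Allowing for the extra variance from mixing two means in the vibration arm lowers the last figure to 70.2%. Restoring 80% at a difference of 4 would take about 100 per arm. Analysing only the 64 observed per arm gives 80.1%, as planned, if losses are unrelated to outcome.

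**3. A change-score analysis instead.** Filled changes are exactly zero, which also reduces the variance. At 20% early loss:

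- SD of change 10: power is 79.3% if the exercise arm does not change and 75.5% if it improves by 5.
- SD of change 7.7 (an assumed baseline correlation of 0.7, since 10 × √(2 × 0.3) = 7.7): power is about 95%.

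The article gives no SD of change, so this cannot be settled from it.

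**4. The 6-month comparison with no true effect.** Assumed, not from the documents: mean 2 points above baseline after training and 3 below baseline at 6 months in both arms, so a fall of 5; all losses fall between the two visits. The spurious difference is 5 × (loss in arm A − loss in arm B), in favour of arm A.

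- 20% vs 20%: 5 × 0 = 0.
- 25% vs 15%: 5 × 0.10 = 0.5 point.
- 30% vs 10%: 5 × 0.20 = 1.0 point.

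For type I error, the average variance per arm is SD² + 25 × the mean of *d*(1 − *d*) over the arms, and the standard error is √(2 × variance/80).

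| Loss | SD | Standard error | Shift/SE | Two-sided rejection |
|---|---|---|---|---|
| 25% vs 15% | 10 | 1.61 | 0.31 | 6.1% |
| 30% vs 10% | 10 | 1.61 | 0.62 | 9.5% |
| 25% vs 15% | 6 | 1.00 | 0.50 | 7.9% |
| 30% vs 10% | 6 | 1.00 | 1.00 | 17.1% |

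Simulated null trials with 80 per arm agree: about 6% and 9% to 10% at SD 10, and about 7% to 8% and 16% to 17% at SD 6. With equal losses the rate does not exceed 5%. A correlation of 0.7 between visits was assumed in the simulations, but it does not affect this raw-score comparison.

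**The case against.** Several stronger readings are tempting, and the documents do not support them.

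- **That the trial fails to deliver 80% power.** A reader might infer this from the 71%. It needs all 20% lost within the six training weeks and a raw-score comparison. The article gives no timing for the losses, and follow-up runs to about 6 months. Power stays above 80% unless more than about 10% are lost before week 6. The planned ANOVA on changes may also do better.
- **That power falls because decliners are scored as stable.** The loss at 6 weeks comes from the zero expected group difference at baseline, whether or not anyone declines. Equal loss and equal decline leave the contrast unbiased. If residents who leave training early truly gain nothing, part of the fall from 5 to 4 belongs to the intention-to-treat effect and is not caused by the rule.
- **That those lost are mainly decliners.** This is plausible, since the article describes frail residents, but it is not stated. The Follow-up section also foresees residents moving to another address.
- **That 6-month false positives are certain to be high.** The trajectory and the unequal losses are assumptions, and an SD of 6 appears nowhere in the documents. At the protocol's SD of 10 the milder scenario is close to nominal. The trial is also sized on the end-of-intervention score, not on the 6-month one.
- **That coding of death or inability to perform is missing.** A condensed article may leave this to the full protocol or analysis plan.

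All of this limits the size of the problem. What stands is that the article does state a missing-data rule, for every outcome and visit, and that the rule is not the one behind the sample size. The per-protocol analysis does not test it. Unequal loss is a real possibility, because the trial is open and only one arm trains on the vibration platform.

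**Conclusion.** The concern holds in a conditional form, as a should-fix. The sample size arithmetic is correct; the carry-forward rule does not match it.

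On the protocol's own inputs, 6-week power for raw Tinetti scores is about 71% if the full 20% are lost before week 6. The shortfall disappears once early loss is about 10% or less. For a change-score analysis the answer depends on an SD that is not given.

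At 6 months the rule can create a difference where none exists, but only if scores fall after training and the arms lose different numbers. Under the assumed 5-point fall, the spurious difference is about 0.5 point with 6% to 8% type I error at 25% versus 15% loss. At 30% versus 10% it is about 1.0 point with about 10% (SD 10) to 16% (SD 6). Under other trajectories the direction could reverse.

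**What to change.** In Statistical methods, replace the carry-forward sentence as follows:

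- **Primary analysis:** a likelihood-based mixed model for repeated measures with the 6-week and 6-month scores as outcomes and baseline, group, visit and group-by-visit as terms, using all observed scores of all randomised residents. Multiple imputation would serve equally well.
- **Sensitivity:** one analysis that lets missing scores be worse than the model predicts (missing not at random). Carry-forward may stay, at most, as a further sensitivity analysis.
- **Timed tests:** state that a Timed Up & Go or Sit-to-Stand that a resident attempted but could not complete is not replaced by an earlier successful time.

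The cost is a reworded paragraph and some programming, with no extra residents, visits or data. With losses unrelated to outcome, analysing observed scores also restores the logic behind the 160. The small downside is that the primary model assumes data are missing at random, which the sensitivity analysis addresses.

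### Carrying the last score forward gives residents lost before 6 weeks a baseline Tinetti score, a dilution that the sample size does not allow for

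*Protocol article*

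**What the plan says.** - **Missing data.** The Statistical methods section sets an intention-to-treat analysis, adds a per-protocol analysis, and fills gaps by one rule: "Missing values will be assigned the last available valid score".
- **Visits.** The Follow-up section states: "All tests will be performed at baseline, at 6 weeks", with one later assessment at 6 months. Nothing is measured between baseline and 6 weeks.
- **Sizing.** The Sample size section works from "assuming a difference of 5 points (SD 10) between the groups in the Tinetti test at the end of intervention". It continues: "We considered a two-sided alpha level of 0.05, a statistical power of 80%, and 20% of losses". The result is given as "The total number of estimated cases was 160 (80 in each group").
- **Tests.** The Statistical methods section offers a t test, a rank test or a chi-square test according to the type of outcome. For changes in body balance and muscle performance it also names a two-way ANOVA with group, time and their interaction.

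**The concern.** The Sample size and Statistical methods sections treat lost residents differently. The allowance for losses presumes that those residents drop out of the comparison and that everyone left shows the full 5 points. The missing-data rule keeps them in. For the 6-week comparison, the only score they can bring is the one taken before training began. Randomised groups do not differ in expectation at baseline, so under equal loss the filled share adds no treatment difference and pulls the estimate down.

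At stake are the size of the effect reported for a primary outcome and the protocol's only power statement. Both arms exercise, so both may improve. If more residents leave one arm than the other, the estimate then depends partly on who left.

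**Working it through.** **Inputs from the Sample size section:** difference 5, SD 10, two-sided 0.05, power 80%, losses 20%, 80 per arm.

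**Step 1. Reproduce the stated number.** The t test with n per arm has noncentrality d / (SD × √(2/n)). With d = 5, SD = 10 and n = 64 this is 5 / 1.77 = 2.83, and power is 80.1%. Then 64 / 0.8 = 80 per arm, or 160 in total, exactly as stated. The normal approximation gives 63 per arm, then 79, or 158 in total. The stated 80% therefore belongs to an analysis of 64 observed residents per arm.

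**Step 2. Apply the missing-data rule.** Let a share L of each arm be lost before 6 weeks, at random. The expected difference is (1 − L) × 5 + L × 0. At L = 0.20 this is 4.0. All 80 per arm are analysed, so the noncentrality is 4 / (10 × √(2/80)) = 4 / 1.58 = 2.53, and power is 71.0% (71.6% by normal approximation). Simulation with 10,000 trials per setting gave 70.7% to 71.0%. Holding 80% power at a 4-point difference would need about 99 per arm, 198 in total (normal approximation).

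**Step 3. Vary the share lost by 6 weeks** (t test on 6-week scores, 80 per arm analysed).

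| Lost by 6 weeks | Expected difference | Power |
|---|---|---|
| 5% | 4.75 | about 85% |
| 10% | 4.50 | about 81% |
| 15% | 4.25 | about 76% |
| 20% | 4.00 | about 71% |
| 25% | 3.75 | about 65% |

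At 10% loss, the observed residents alone would give about 85% (normal approximation). The rule has a cost there too, although the stated 80% is still met.

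**Step 4. Change scores, or the group-by-time interaction.** This needs the correlation r between baseline and 6 weeks, which the protocol does not give. Assume r = 0.6. The variance of change is then 2 × 100 × (1 − 0.6) = 80. A filled resident has a change of exactly zero, so each arm's variance becomes 0.8 × 80 + 0.8 × 0.2 × (mean gain)².

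- *No control gain:* variances 64 and 64 + 0.16 × 25 = 68. The standard error is √(132/80) = 1.28, and 4 / 1.28 gives power of about 88%. The 64 observed per arm give about 89%, so the cost is about 1 point.
- *Common gain of 5 (assumed):* variances 64 + 0.16 × 25 = 68 and 64 + 0.16 × 100 = 80. The standard error is √(148/80) = 1.36 and power is about 84%, so the cost is about 5 points.

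In both cases the estimate is 4.0 instead of 5.0.

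**Step 5. Unequal loss.** Assume a common gain of 5, so the true mean gains are 10 with vibration and 5 without.

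- 10% lost with vibration and 30% in control: 0.9 × 10 − 0.7 × 5 = 5.5.
- 30% lost with vibration and 10% in control: 0.7 × 10 − 0.9 × 5 = 2.5.

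The true difference is 5.0 in both.

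**The case against.** Four counter-arguments carry weight.

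1. **The 71% belongs to one of two named analyses.** The t test comes from a list that serves all outcomes, while the ANOVA is named specifically for changes in body balance. Step 4 shows that the ANOVA, read as a comparison of change, loses little power. This stands: a reader might infer that the trial as a whole has 71% power, and the protocol does not support that. But the 71% does apply to the end-of-intervention comparison on which the trial was sized, and the dilution to 4.0 occurs under either analysis.

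2. **The timing of losses is not stated.** Follow-up runs to 6 months, and some of the 20% may leave after the 6-week test. This also stands as a limit: with about 10% or less lost by 6 weeks, the stated 80% is met. Placing all 20% before 6 weeks is nevertheless the natural reading of an allowance attached to an end-of-intervention difference.

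3. **Filled values might seem to make the standard error too small.** A reader could compare 1.58 (80 per arm) with 1.77 (64 per arm) and conclude this. It does not follow, because the two figures belong to different estimators. Each filled resident still contributes one independent value. In simulation the mean t-test standard error was 1.59 against an empirical 1.58 to 1.60, and the type I error was about 5% under equal loss.

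4. **Bias towards no difference is not general.** This stands, as Step 5 shows. It weakens any claim that the rule is merely conservative.

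The added per-protocol analysis does not answer the point, because it leaves the main intention-to-treat estimate as it is.

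**Conclusion.** The point holds in conditional form. The missing-data rule and the sample size describe different analyses, and the stated power allows only for the one in which lost residents are left out. With 20% lost by 6 weeks, equally and at random, the expected Tinetti difference is 4.0 instead of 5.0, and the t test on 6-week scores has about 71% power instead of 80%.

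These figures assume that SD 10 is the SD of the score, as the Sample size section reads, and that the control arm gains little. With a common gain of 5, power of that t test falls to about 67%. If SD 10 were instead the SD of change, power would be about 80% with no control gain and about 76% with a common gain of 5.

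This should be fixed before analysis. It does not put the design in doubt, and under equal random loss it does not raise the false-positive rate.

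**What to change.** Replace last-score filling as the main method for the Tinetti test, Timed Up & Go and Sit-to-Stand. Use a likelihood-based repeated-measures (mixed) model on all observed scores of all randomised residents at baseline, 6 weeks and 6 months. Keep last-score filling at most as a sensitivity analysis. With 160 residents this meets the stated 80% if losses are at random given the observed scores. In a frail population that condition is an assumption and should be stated as one.

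If the rule stays as the main method, restate the power of the 6-week t test as about 71% at 20% loss, and say that the estimate is diluted under equal loss and can be biased either way under unequal loss.

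The cost is wording in the statistical section only: no new data, visits or residents.
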